## Abstract

**Background:**

Influenza vaccination confers broad benefits in the elderly and certain high-risk populations, but its effectiveness in patients with acute heart failure (HF) is uncertain. Rates of influenza vaccination are low in China due to poor awareness, cultural misunderstandings, and cost.

**Aims:**

To determine the effectiveness of influenza vaccination in patients with acute HF admitted to hospitals in China.

**Methods:**

The second Population Assessment of Influenza and Disease Activity (PANDA II) study is a two-arm, parallel-group, county-level hospital-based, cluster randomized controlled trial to determine the benefits and risks of full access to routine free influenza vaccination before hospital discharge, compared to routine limited use of influenza vaccination, on the primary endpoint of death or hospital readmission. Consecutive hospitalized patients at each site are enrolled to a target of 50 participants in each autumn–winter influenza outbreak period (October to March) over 3 consecutive years to reach the required sample size. Patients are centrally followed up at 1, 3, 6, and 12 months after hospital discharge (or death if earlier). Site numbers varied across year according to predicted influenza activity and logistical reasons.

**Conclusions:**

This study offers a unique chance to clarify uncertainties surrounding the effectiveness of influenza vaccination in patients with HF and to lay the groundwork for future prevention strategies.

**Trial registration:**

This trial was registered with the acronym PANDA II (Population Assessment of Influenza and Disease Activity) at ChiCTR.org.cn (ChiCTR2100053264). Registered on 17 November 2021.

**Supplementary Information:**

The online version contains supplementary material available at 10.1186/s13063-024-08452-8.

## Introduction

### Background and rationale {6a}

According to World Health Organization (WHO), influenza causes a severe illness in approximately 3 to 5 million people and results in 290,000 to 650,000 deaths each year [1]. Older people and those with cardiovascular (CV) disease are more likely to suffer a severe illness [2, 3]. Heart failure (HF) is a major clinical and public health concern that is estimated to affect 1.3% (13.7 million) of adult (age ≥ 35 years) population of China [4]. Patients who are hospitalized for HF have a high case fatality [5]. In Veterans Affairs Health Care System, the overall unadjusted rates of 1-year death or hospital readmission are 25.0% and 61.4%, respectively [6]. Up to one third of hospitalized cases of HF are triggered by respiratory infection [7], often from influenza [8], and this contributes to the poor outcome [9].

Influenza vaccination is a key management strategy in patients with CV disease [10]. In the Influenza Vaccination After Myocardial Infarction (IAMI) study involving 2532 patients, influenza vaccination produced a significant 28% relative reduction in the risk of the composite endpoint of all-cause death, myocardial infarction (MI), or stent thrombosis at 12 months [11]. Although guidelines and the World Health Organization recommend the use of influenza vaccination to improve survival after HF [12], the only randomized controlled trial (Influenza vaccine to prevent adverse vascular events [13]) failed to show a clear reduction in the primary endpoint of CV death, MI, and stroke, although there were 22% and 16% reductions in deaths and hospitalizations in the peak influenza seasons during follow-up. Influenza vaccination rates vary greatly across the world, from approximately 60% in patients with HF in Western Europe and the US [14], to less than 1% in China [15]. The low rate of vaccination in China can be explained by being an out-of-pocket expense [9], cultural beliefs, poor awareness [16], and safety concerns [14, 17].

The PANDA II study aims to provide evidence of the effectiveness of influenza vaccination for improving outcomes in patients with severe HF, using a hybrid effectiveness-implementation design. The feasibility in ensuring high levels of influenza vaccine coverage rates (VCR) in routine practice was confirmed in a pilot phase to the study in which 518 participants were recruited at 11 hospitals in the Henan Province of China between December 28, 2020, and January 29, 2021 [17].

### Objectives {7}

The objective is to determine whether the provision of free influenza vaccine before discharge from hospital has a beneficial effect on all-cause mortality or hospital readmission, compared to routine care, in patients with severe HF.

### Trial design {8}

This is a two-arm, parallel group, cluster-randomized 1:1 controlled trial designed to determine whether a program of free influenza vaccination in hospitalized HF patients improves outcome compared to usual standard of routine care. The unit of randomization is the hospital where investigators are required to enroll consecutive patients with HF during a defined winter period. Hospitals are centrally randomly allocated to be an intervention arm to provide a free influenza vaccination in wards devoted to the care of patients with HF. The control hospitals are to provide usual standard of care without routine Point of Vaccination (POV) but can make recommendations to patients to receive their influenza vaccination at community health care center. This crossover may reduce the study’s ability to detect the vaccination’s effect. To account for this, we estimated that 10% in the control group would receive the vaccine and adjusted the sample size accordingly. The study was planned to be undertaken in phases over three years and for participating hospitals to be re-randomized before each winter recruitment period. A detailed flowchart is shown in Fig. 1.

**Fig. 1 Fig1:**
[figure not shown]
PANDA II main trail schema

## Methods: participants, interventions, and outcomes

### Study setting {9}

The study is undertaken in county-level hospitals which serve relatively fixed local populations to avoid the risk of contamination. They are located in the geographically dispersed regions of the provinces of Henan, Jilin, Hebei, Shaanxi, Hunan, and Guangxi, to enhance the generalizability of the results (Appendix: participating hospitals). Up to 60 hospitals are randomly assigned to intervention or control groups in each year. At the completion of each recruitment period, an assessment is made of the recruitment volume, adherence to the protocol, and completeness of the data, to decide on their continued participation.

### Eligibility criteria {10}

#### Hospital-level inclusion criteria

Hospital sites are eligible if they meet all following requirement:Ability to manage a high volume of patients with HF;Capacity to enroll a target of 50 participants in a recruitment period;Adequate levels of staff to participate in research;Approval from the local government to provide influenza vaccination in the hospital.

#### Hospital-level exclusion criteria

Hospital sites are not eligible if they meet any of the following criteria:
Participation in another influenza vaccination-related program;A policy of free influenza vaccination was already available for local residents.

#### Individual-level inclusion criteria

Patients are eligible if they meet all the following requirement:Age ≥18 years;Admission for hospital with a diagnosis of HF;Severity of HF that is grade III or IV in the New York Heart Failure classification system;Recruitment is to be consecutive to the quota of 50 participants;Provision of written informed consent.

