## Interventions

### Intervention description {11a}

POV for influenza vaccination will be established in all study centers allocated to the intervention group. All participants receive vaccine of  the Sanofi Pasteur trivalent inactivated influenza vaccine (0.5 ml) or vaccine from another manufacturer with comparable efficacy within 24 h before discharge from hospital. The intervention involves education and training of the healthcare team in vaccination procedures. Patients eligible for the study who consent to follow-up will be enrolled regardless their wiliness to be vaccinated. Routine standard of care procedures is to be maintained for both groups. No intervention will be applied to the control arm but patients will be encouraged to seek influenza vaccination at a community health center or immunization clinic.

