## Data collection and management

### Plans for assessment and collection of outcomes {18a}

Data collection for both groups will be conducted concurrently and in parallel. Screening and baseline data will be collected and documented at the time of admission and during hospitalization by the pre-specified research team at each site. The population descriptive information, including demographics, anthropocentric, medical history, and concomitant medications, is collected by self-report. Results of laboratory test including blood, urine sampling, and echocardiogram will be retrieved. The electronic health records will be searched for source data validation, if available. Patients will be surveyed with quality of life and mood questionnaires: EQ-5D [19] and PHQ-9 [20]. Influenza vaccination data will be obtained prior to discharge. Centralized follow-up will be conducted by the coordinator center at each follow-up period to obtain information on deaths, re-hospitalization, occurrence of ILI, and any SAEs, along with the use of specific HF medications.

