#### Endpoint analysis

The aim of the primary analysis will be to establish whether there are benefits in all-cause mortality or all-cause hospital readmission within 1 year (excluding events within 30 days post-discharge or occurring during a non-influenza season) from patients enrolled in the intervention hospitals compared with patients enrolled in the control hospitals. Aggregate cluster-level mean rates of primary endpoints between intervention clusters and control clusters will be compared by Wilcoxon rank-sum test. The intention-to-treat (ITT) principle will be applied.

In the secondary analysis, generalized linear mixed model will be performed to allow for the clustered nature of the data and to adjust the cluster-level covariates including province, hospital, and phase.

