## Discussion

The PANDA II study aims to provide direct and reliable evidence on the effectiveness and safety of influenza vaccination in patients with acute HF. It follows the implementation strategy proposed in a pilot study [17], where a 90% vaccination coverage rate (VCR) was achieved in the intervention group, and remained as low as < 1% in the control group as influenza vaccines are not covered by the national immunization program in regions of China [16]. A strength of this trial is the design, which provides an exceptional opportunity to evaluate both efficacy and policy perspectives regarding the protective effect of influenza vaccination in patients with HF.

Another strength of this trial lies in its recruitment strategy, which leverages the existing HF health provider network and ensures the inclusion of consecutive and representative participants. The construction of POV in hospitals during the trial enhances the intervention implementation and site adherence, which can be scaled up into a routine practice should the intervention prove to be effective. Despite encountering logistical challenges associated with the conduct of such a large cluster trial in a range of low resource settings where there are varying levels of trial experience, our research team has implemented centralized monitoring and tracking systems for participating hospitals and patients to ensure data quality. Furthermore, the study faced difficulties due to the COVID-19 pandemic. It can be expected that the outcome event rates will differ according to times of co-circulation the COVID-19 virus and influenza activity was low in the period of quarantine policy in 2021. We did not initiate the study until the influenza activity surveillance reported an ILI + /ILI > 3% at week 38 of 2021. In 2022, a higher mortality rate in patients with HF was observed due to COVID-19 infection, which may dilute the effect of influenza vaccination. However, stratified cluster randomization design is expected to keep the influence balanced between study arms. A sensitivity analysis will be performed to evaluate the impact of COVID-19.

Our study is a well-powered and on schedule to resolve uncertainty over influenza vaccination in an effectiveness-implementation hybrid design, while also providing a model for future preventive strategies in patients. Insights gained from this study will inform and enhance HF management practices in regions where influenza vaccine uptake remains low.

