## Trial status

The study has received approval from relevant ethics committees and regulatory bodies at both national and local levels in China. Patient enrollment began on December 1, 2021, and concluded on February 8, 2024. The current protocol is version 3.0 (date: April 30, 2024), and all protocol amendments have been approved by study steering committee and Medical Ethics Committee of Beijing Anzhen Hospital affiliated to Capital Medical University (Research Ethics Review (2021) No.18) and communicated with investigators and DSMB members.

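### The season-bound primary endpoint can depend on discharge date within October to March, and no stated analysis accounts for that date

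*Protocol article*

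**What the plan says.** All places are in the protocol article.

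- **Recruitment.** The abstract's Methods has patients "enrolled to a target of 50 participants in each autumn–winter influenza outbreak period (October to March) over 3 consecutive years". The individual-level inclusion criteria add: "Recruitment is to be consecutive to the quota of 50 participants". No common opening date or pace is stated for the sites.
- **Set-up.** Under Intervention description {11a}: "POV for influenza vaccination will be established in all study centers allocated to the intervention group". Control hospitals have no such step.
- **Endpoint.** Outcomes {12} counts death or hospitalization in the influenza season within one year of discharge and leaves out the first 30 days. Its rationale also says that events after the corresponding season are unlikely to be preventable. It does not settle whether days in the following season count.
- **Analysis.** Endpoint analysis compares cluster-level mean rates by a Wilcoxon rank-sum test with no covariates. The secondary mixed model is to "adjust the cluster-level covariates including province, hospital, and phase".
- **Timing.** The Discussion says: "It can be expected that the outcome event rates will differ according to times of co-circulation". Trial status says: "Patient enrollment began on December 1, 2021, and concluded on February 8, 2024".

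**The concern.** A patient discharged in October spends most of the countable season in the first half of follow-up. A patient discharged in February spends most of it 8 to 12 months after discharge or, on the narrower reading, has almost no countable time. If risk is higher soon after discharge, or if only the enrolment season counts, two groups with identical prognosis and no vaccine effect would have different expected rates merely because they were discharged at different dates.

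Date differences unrelated to allocation add between-cluster noise. Differences caused by allocation add bias. The one step in the text that could cause such a difference is setting up the vaccination point, which falls on intervention sites only. If it delayed their enrolment, the intervention rate would be lowered and the vaccine would look better than it is. The phase covariate separates seasons, not dates within a season.

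**Working it through.** **Yardstick.** The inputs are in Sample size {14}: infection 15%, endpoint risk if infected 80%, vaccine protection 60%, coverage 90% v 10%, control rate taken as 50%.

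- Infection in control: 0.15 × (1 − 0.10 × 0.60) = 14.1%.
- Infection in intervention: 0.15 × (1 − 0.90 × 0.60) = 6.9%.
- Planned difference: 0.80 × (14.1 − 6.9) = 5.76 points.

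With an ICC of 0.03 and 45 evaluable patients per hospital, these inputs give 164 hospitals for 90% power, not 122. That is a separate matter; only the difference is used here.

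**Days at risk.** Assume a season of 1 October to 31 March and count season days from day 31 to day 365.

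| Discharge | All season days in the year | In days 31–180 | In days 181–365 | Enrolment season only |
|---|---|---|---|---|
| 1 Oct | 152 | 150 | 2 | 151 |
| 1 Nov | 152 | 120 | 32 | 120 |
| 1 Dec | 152 | 90 | 62 | 90 |
| 1 Jan | 152 | 59 | 93 | 59 |
| 1 Feb | 152 | 28 | 124 | 28 |
| 1 Mar | 152 | 0 | 152 | 0 |

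On the literal wording the total is constant and only its position moves.

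**One delay by hand.** Let the hazard in days 31–180 be k times that in days 181–365. Weighted days are W = k × (early days) + (late days), and risk = 1 − exp(−cW). Set c so that a 1 December discharge has 50% risk, then move discharge to 15 December (76 early and 76 late days).

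- k = 1: W is 152 on both dates; no shift.
- k = 1.5: W goes from 197 to 190; risk = 1 − exp(−0.693 × 190/197) = 48.8%, a fall of about 1.2 points.
- k = 2: W from 242 to 228; risk 47.9%, a fall of about 2.1 points.
- k = 3: W from 332 to 304; risk 47.0%, a fall of about 3.0 points.
- Enrolment season only, flat hazard: 90 days to 76; risk 44.3%, a fall of about 5.7 points.

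**Whole recruitment block, all season days counted.** Take 90 days of discharges from 15 October, with c set so that mean risk over October to March is 50%.

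| Assumed hazard | Fall, 2-week lag | Fall, 4-week lag |
|---|---|---|
| Flat | 0 | 0 |
| Step, k = 1.5 | 1.3 | 2.6 |
| Step, k = 2 | 2.1 | 4.3 |
| Step, k = 3 | 3.2 | 6.6 |
| Weibull, shape 0.8 | 0.6 | 1.3 |
| Weibull, shape 0.7 | 0.9 | 1.9 |
| Weibull, shape 0.6 | 1.1 | 2.4 |

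A 45-day block from 1 December gives somewhat larger falls: 1.0 and 2.3 points at shape 0.7.

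**Enrolment season only.** The December block at 50% risk falls by 6.9 to 7.8 points for a two-week lag (shape 0.7 and flat hazard). At 30% risk the fall is 4.8 to 5.4 points.

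**Consequence for the test.** Take 61 clusters per arm, 45 patients each, ICC 0.03. The standard error is √(2 × 0.25/45 × (1 + 44 × 0.03)/61) = 2.06 points. Under no vaccine effect, a false difference of 0.6, 1.3 or 3.2 points raises the two-sided 5% error to about 6%, 10% or 34% (normal approximation).

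**The case against.** The other side has substantial points.

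- **No lag is documented.** A reader might infer that intervention sites started later and that the result is therefore biased towards the vaccine. The text does not show this. Nothing says that enrolment waits for the vaccination point. Every site must already have "Approval from the local government to provide influenza vaccination in the hospital". Re-randomization in later seasons precedes the recruitment window, and "Data collection for both groups will be conducted concurrently and in parallel". These passages make a long lag less likely, but none fixes enrolment dates by arm. The 1 December 2021 start is for the trial as a whole.
- **The dependence is not built in.** A reader might also take discharge date to drive the endpoint by definition. On the literal wording it does not: season days are equal for first-of-month discharges, and a flat hazard gives no shift. The hazard shapes above are assumptions; the article gives no figure.
- **Randomization balances site pace.** Allocation stratified by province and repeated each season balances pace in expectation. This stands for pace unrelated to allocation. It does not cover delay that allocation itself causes.
- **COVID-19 timing.** The Discussion's examples concern years, and a sensitivity analysis is planned, so that sentence lends only limited support.
- **The analysis plan may say more.** It is not shown, and the covariate list is open-ended. The point is therefore confined to what the article fixes: a primary test without covariates and named covariates that do not include date within a season.

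**Conclusion.** The point holds as a modest, conditional weakness. The expected primary rate can depend on discharge date: strongly if only the enrolment season counts, modestly on the literal wording with a declining hazard, and not at all with a flat one. For a two-week lag, the declining hazards tried give 0.6 to 3.2 points, or about a tenth to just over half of the planned 5.76. The narrower season reading could exceed the planned difference.

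These sizes rest on an assumed October to March season, assumed hazard shapes, a 50% mean risk and a hypothetical lag. The article does not support a claim that the trial is biased. It supports the statement that discharge dates could differ between arms, and that neither the primary test nor the covariates named for the model would reveal or correct it. Without a lag, unmodelled date differences still cost some precision.

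**What to change.** In Endpoint analysis:

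1. Add discharge date to the mixed model as a patient-level covariate, either as calendar month within season or as a spline of days since 1 October.
2. Report the distribution of discharge dates by arm and season.
3. Add a sensitivity version of the cluster-level comparison. For example, obtain each patient's expected risk from a model with discharge date and season but not arm, take observed minus expected events per cluster, and apply the same Wilcoxon test. This is needed because the mixed model leaves the primary test unchanged.

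Follow-up is timed from discharge, so the date should already be held for every participant. The cost is wording and a few degrees of freedom. If the arms match on date, the table answers the concern. If they barely overlap in part of a season, adjustment would extrapolate and should be read with that in mind. Stating whether the following season's days count would settle which of the sizes above applies. A common opening date for both arms is no longer an option, because enrolment has closed.

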#### Individual-level exclusion criteria

Patients are not eligible if they meet any of the following criteria:Previous enrollment in the study;≥ 2 admissions to hospital with HF in the past 2 months;Known allergy to influenza vaccine;Vaccination for COVID in the past 14 days;Discharge from hospital with the intention of being transferred to another medical facility for further treatment.

## Who will take informed consent? {26a}

### Consent process for hospitals

Sites are required to consent patients prior to undertaking any study procedures including randomization. The process of consent has the approval of the General Manager or Head of the Cardiology Department.

### Consent process for individuals

Participants in the intervention arm provide consent for both vaccination and follow-up, whereas those in the control arm only provide consent for follow-up. Potential participants receive written information on the study and are given sufficient time to ask questions and make their decision. Refusal to participate does not influence the management of patients. Only patients with a signed informed consent are enrolled in the study. No study procedures or intervention will take place until the informed consent procedure is complete.

### Additional consent provisions for collection and use of participant data and biological specimens {26b}

This study does not involve any preservation or use of biological specimens.

## Interventions

### Intervention description {11a}

POV for influenza vaccination will be established in all study centers allocated to the intervention group. All participants receive vaccine of  the Sanofi Pasteur trivalent inactivated influenza vaccine (0.5 ml) or vaccine from another manufacturer with comparable efficacy within 24 h before discharge from hospital. The intervention involves education and training of the healthcare team in vaccination procedures. Patients eligible for the study who consent to follow-up will be enrolled regardless their wiliness to be vaccinated. Routine standard of care procedures is to be maintained for both groups. No intervention will be applied to the control arm but patients will be encouraged to seek influenza vaccination at a community health center or immunization clinic.

